#### Acceptability

We measure acceptability around these factors, including how connected (1 not at all connected to 10 very connected), how meaningful was the KIND Challenge activity (1 not very meaningful to 10 very meaningful), how safe they felt when completing the KIND Challenge (1 not very safe to 10 very safe), how positive they felt (1 not very positive to 10 very positive), how comfortable they felt doing the KIND Challenge activity (1 not at all comfortable to 10 very comfortable). It is anticipated that the Nextdoor KIND Challenge will yield ratings of more than 5 indicating higher levels of acceptability across these outcomes. These questions were specifically developed for the study (see Supplementary Table 1 section c).

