#### Safety

We assess for unintended harms (e.g., conflict) during this period. In this case, we measure the occurrence of neighbor conflict because of the KIND Challenge. It is anticipated that the KIND Challenge activity is safe for participants with no unintended conflicts reported. This question was developed for the study (see Supplementary Table 1 section d).

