For feasibility, acceptability, and safety, we will present the descriptive statistics on these indicators (feasibility = < 40% drop out; acceptability more than 5 or higher on meaningful, safe, positive, and comfort ratings; and no reported conflicts because of doing the KIND challenge).

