#### Serious adverse events

An adverse event within this study is defined as participants reporting more than discomfort (e.g., distress) over a particular aspect of the current study. Due to the nature of the survey questions as well as the nature of the KIND Challenge (i.e., doing acts of kindness), we anticipate minimal risk to participants. Participants will be asked questions about their mental health but are not coerced into answering questions and can skip a question or close the survey at any time. Participants will be encouraged to seek counselling and support services if they feel they need someone to talk to. Participants will also have to the research team and ethics officer’s details should they choose to discuss any potential risk issue. The number for each country’s crisis service will also be provided in the participant information and consent form as an additional safety measure. If a participant opts for direct assistance and permits us to contact, we can debrief the participant and refer appropriate country specific services.

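### The safety indicator counts only neighbour conflict caused by the Challenge and leaves out the protocol's own adverse events and its felt-safety rating

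*Protocol article*

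**What the plan says.** The Abstract and the Objectives name safety, with feasibility and acceptability, as something the trial will assess. Four places in the protocol article bear on how.

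- **Safety (Implementation secondary outcomes).** The aim is broad: "We assess for unintended harms (e.g., conflict) during this period". The next sentence narrows the measurement: "In this case, we measure the occurrence of neighbor conflict because of the KIND Challenge". The expectation then links the word safe to that one measure: "It is anticipated that the KIND Challenge activity is safe for participants with no unintended conflicts reported".
- **Secondary outcomes analysis.** Feasibility, acceptability and safety are to be described, and the safety indicator is "no reported conflicts because of doing the KIND challenge".
- **Serious adverse events.** A different concept of harm appears: "An adverse event within this study is defined as participants reporting more than discomfort (e.g., distress) over a particular aspect of the current study". Neither of the two sections above refers to it.
- **Acceptability.** One of the ratings is "how safe they felt when completing the KIND Challenge (1 not very safe to 10 very safe"). The expectation is that the Challenge "will yield ratings of more than 5 indicating higher levels of acceptability across these outcomes". The analysis section names the safe rating among the acceptability ratings, but adds the words or higher to the same threshold, so the standing of a score of exactly 5 is unclear.

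Table 1 schedules the Safety item once, at T3 (post intervention).

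**The concern.** The document has three measures that could show harm, and they pick out different people. Only one of them, conflict attributed to the Challenge, decides the safety indicator. A participant who was distressed by taking part, or who gave the lowest score for feeling safe, meets the indicator as long as no neighbour conflict is reported.

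This matters because safety is a stated objective, and the activity is carried out with neighbours during a pandemic. A report that the Challenge is safe would be read as covering harm in general. On the indicator as fixed, it would mean only that nobody reported a conflict with a neighbour because of the Challenge.

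**Working it through.** The plan gives no rate or sample-size figure for safety, so there is none to reproduce. The check sets the measures side by side and then sizes the gap.

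**What each measure counts**

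| Measure | What counts | How it is obtained | Where it is used |
|---|---|---|---|
| Challenge conflict | Neighbour conflict because of the Challenge | Survey item at T3 | Safety indicator (zero reports) |
| Adverse event | More than discomfort over some aspect of the study | Participant chooses to contact the team | Not in the safety outcome or its indicator |
| Felt safety | Rating from 1 to 10 | Survey, after the Challenge | Acceptability only |

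**How individual cases fall**

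- Conflict because of the Challenge, no distress, high safe rating: the indicator fails.
- Distress meeting the adverse-event definition, no conflict: the indicator is met.
- Safe rating of 1, no conflict: the indicator is met; the rating appears under acceptability.
- Distress followed by withdrawal before T3: no answer to the conflict or safe items, so the indicator is not affected. Of the three measures, only an adverse-event report could record this person.

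**Inputs.** 1500 participants per country (Sample size) and 1:1 allocation (Allocation and blinding) give 1500 / 2 = 750 in the Challenge arm. Feasibility allows drop-out below 40%, so at that limit 750 × 0.60 = 450 would answer at T3. Waitlist participants also do the Challenge later; these figures leave them out.

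**Distress (assumed rates, since the document gives none).** 750 × 0.02 = 15 and 750 × 0.05 = 37.5, so about 15 to 38 people per country. The rate does not matter to the logic: these events are not part of the indicator, so no number of them changes it.

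**Conflict.** With a true per-person reporting rate p and n respondents, the chance of zero reports is (1 − p)^n.

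| p | n = 750 | n = 450 |
|---|---|---|
| 0.1% | 0.47 | 0.64 |
| 0.5% | 0.02 | 0.10 |
| 1% | 0.0005 | 0.01 |

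For conflict the criterion is therefore strict. If it is met, the exact one-sided 95% upper bound on the conflict rate is 1 − 0.05^(1/n): 0.40% for 750 respondents and 0.66% for 450. That is what the indicator can establish. It says nothing about the other two measures.

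**Felt safety.** The document does not say how the rating is summarised. If a mean across participants were used, 40% scoring 1 and 60% scoring 9 would give 0.4 × 1 + 0.6 × 9 = 5.8. That passes a threshold of more than 5 with 0.4 × 750 = 300 people at the lowest score. A frequency table would show those people plainly. This is a reason to state the summary, not evidence of what is planned.

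**The case against.** The best defence is that the sections do different jobs. The adverse-event text sits under oversight and concerns participant protection: skipping questions, crisis numbers, debriefing and referral. It covers the survey questions as well as the Challenge. The Safety outcome concerns the Challenge alone. How adverse events are logged and tabulated is normally left to a fuller document, and felt safety is a perception that can reasonably sit under acceptability. The arms are also compared on depression, social anxiety and stress (H4) and on past-month neighbour conflict (H3e), so average worsening could be seen.

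Much of this stands. The missing tabulation detail is not counted here. It does not remove the mismatch, because the article itself sets the aim as unintended harms, measures one kind, and links safe to that kind alone. The H4 and H3e comparisons are efficacy analyses of groups; they do not count individuals harmed by taking part.

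A reader might infer two stronger things, and neither is supported:

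- **That the safe rating is averaged into acceptability, which hides people who felt unsafe.** No section pools the items or averages participants. The analysis section promises descriptive statistics, so the safe rating would still be presented.
- **That the Challenge could be called safe whatever harm is reported.** A single report of Challenge conflict defeats the criterion, and the analysis is descriptive with no formal declaration rule. The gap concerns harms other than conflict.

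**Conclusion.** The point holds in limited form. The safety indicator is narrower than the aim stated in the Safety section and narrower than the protocol's own definition of an adverse event, and the one direct rating of felt safety counts elsewhere. For harms other than conflict, the indicator can be met at any frequency of distress or of low safe ratings.

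The logical gap follows from the text alone. Its practical size is unknown: the 15 to 38 people per country rest on an assumed 2% to 5% distress rate and full response from 750 participants, and the 5.8 example rests on an assumed distribution and an assumed mean. The primary analysis of loneliness is not affected. What is at stake is what the trial may say about safety, and correcting it costs little.

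**What to change.** Reconcile the Safety section and the safety indicator in the Secondary outcomes analysis with the definition under Serious adverse events. Report under safety:

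1. conflict because of the Challenge, as now;
2. the number of adverse events as the protocol defines them, by arm, with the period shown because the waitlist arm starts the Challenge after four weeks, and labelled as voluntarily reported and so possibly incomplete;
3. the distribution of the T3 safe rating, with the share of respondents at or below one stated cut-off.

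The third item requires the two threshold wordings, in the Acceptability section and in the analysis section, to be made the same, so that it is clear whether a score of 5 passes.

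If the indicator is to stay as it is, limit the conclusion to no Challenge-related neighbour conflict having been reported, and do not call the Challenge safe on that basis.

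The cost is some rewording and one more descriptive table. The safe rating is already collected. Adverse-event counts need contacts with the team to be recorded as data, which the article does not say is done. The safety summary may look less favourable.

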### Adherence and engagement variability

Variability in adherence and engagement will be measured in the participants allocated to the KIND Challenge group. First, adherence can be measured by the frequency and duration of KIND acts completed during the 4-week intervention. Second, an index of level of engagement for each type of activity completed (i) emotional support, (ii) tangible support, (iii) informational support, and (iv) belonging support, (v) companionship support can be created by combining the frequency and duration to produce an indicator of dosage for each type of KIND act. Third, the impact of overall engagement with the KIND Challenge can be modelled via meaningfulness, degree of positive feelings and sense of connectedness to others.

Linear multiple regression modelling in Mplus 8.3, will be employed to model the adherence and engagement as predictors of post 4-week intervention outcomes (H7), across the primary outcome of loneliness, and secondary outcome of social isolation, a neighbourhood relationship quality and contact, neighbourhood connectedness, and mental health. As with the H1–4 the model building approach will be used.

Reasons for non-compliance will also be captured and explored to assess barriers and challenges to competing the KIND activity, as measured by frequencies of lack of time, forgot, illness, work stress, family pressures or other.

CACE estimation will be employed using Mplus 8.3 to examine whether the effects noted in ITT analyses (H1–4) change once intervention compliance is taken into account. Participant demographics and baseline outcome variables will be used as predictors of the latent class compliance variable. Compliance will be assessed via dosage (i.e., number of kind acts completed; compliers vs. non-compliers). The CACE analysis will follow the same regression model building approaches detailed in H1–4.

### Additional analyses

The exploratory questions will be addressed to determine country differences on loneliness, social isolation, and levels of engagement with the KIND Challenge. MANOVAs and effect size differences will be reported. How loneliness and social isolation differ across neighbourhood characteristics (urban vs rural) and demographic variables (age, gender, socioeconomics) will also be explored. Two regression analyses will be run with loneliness and social isolation as respective outcomes and predictor variables of neighbourhood characteristics (urban or rural) and demographic variables of age, gender and socio-economic status added.

To account for the climate and context the data was collected in, how the COVID-19 pandemic has impacted loneliness and social isolation, and people’s interactions with their neighbours will be explored. Regression analyses will be run with baseline loneliness and social isolation, and baseline neighbourhood relationship quality outcomes: social cohesion and trust, perception that their neighbourhood is improving, importance around getting to know their neighbours, supportive, aversive, or ambivalent neighbour network classification, and neighbourhood conflict; and predictor variables of level of social restriction (i.e., social distancing, quarantine, social isolation, none applicable), number of government restrictions imposed (from a list of 13 types of restrictions), and the change in the amount of face-to-face interaction because of the COVID-18 pandemic (ranging from 1: interacting with almost no one face to face to 5: I have interacted with many more people face to face).

### Missing data

The proportion of missing data will be determined for a given outcome variable and the following procedures will be applied: i) if less than 5% of data are missing a complete case analysis will be undertaken, ii) if more than 5% and is missing and is missing at random (MAR), then multiple full information maximum likelihood (FIML) will be utilised [59, 60]. Post-trial, the extent and nature of missing data will be established, and differences between complete and missing cases will be examined to establish any pattern to the missingness [60]. Logistic regression will be used to predict missingness, whereby each participant will be coded as having complete (0) or incomplete (1) outcome data for loneliness and social isolation, with other study data as explanatory variables (e.g., trial group allocation, gender, age group, baseline scores on depression, social anxiety, QoL, positive affect, stress, neighbourhood relationship quality and contact variables). Where applicable FIML under the missing at random assumption will be utilised in Mplus 8.3. This will enable us to include both partially and completely observed cases of all participants in the analysis, thereby reducing the bias associated with attrition.

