### Sample size

Because there are no large-scale community-led randomised controlled trial interventions with reducing loneliness as a primary outcome, we had to estimate power based on the number of participants and maximum number potential covariates we will need to account for. Power calculations were calculated using PowerUp! [50]. Power was set at 0.80 and an Alpha threshold of 0.05. Estimated pre-post correlations for loneliness are between .35 and .83 [51, 52] and for a conservative estimate the lowest correlations for each outcome are used. Therefore, for a projected sample of 1500 participants per country and with up to 20 co-variates for the primary outcomes of loneliness, a minimum detectable effect size (MDES) for a trial effect is .14 in an intention-to-treat (ITT) analysis. Given recent recommendations that Cohen’s effect size benchmarks are too stringent to detect important effects in social and personality psychology [53, 54], we see an effect size of .14 being of small-medium size that is of some explanatory and practical use, even if only in the short-term and therefore clinically meaningful. Further, noting that the strength of an intervention is best evaluated in relation to outcomes it aims to achieve [55], we are guided by a meta-analysis of loneliness intervention trials that found a mean intervention effect size of − 0.198, but with much variability (95% CI: − 0.32, − 0.08; [56]). Thus, previous research has typically found small-medium effects on average for loneliness interventions and this study is sufficiently powered to detect effects of a comparable magnitude.

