### Statistical methods

All analyses will be conducted individually for each country to reflect differing responses to COVID-19 related social restrictions in place during the intervention. This means that there will be three separate randomised controlled studies. Initial screening will be conducted to check normality and score distribution (e.g., skew and kurtosis) on all outcome variables. Where data distributions fall outside of acceptable levels of normality, subsequent analysis will account for that using non-normality robust estimators (such as the Mplus estimator MLR; [57]). To ensure randomisation was successful, balance at baseline will be assessed between the trial and control group on all outcomes i.e., primary outcome loneliness, secondary outcome social isolation, and secondary neighbourhood relationship quality and contact outcomes (c) social cohesion and trust, (d) perception that their neighbourhood is improving, (e) importance around getting to know their neighbours, (f) supportive, aversive, or ambivalent neighbour network classification, (g) neighbourhood conflict, (h) number of neighbourhood contacts, and the secondary mental health outcomes, (i) depression, (j) social anxiety, (k) stress, (l) quality of life, and (m) positive affect. MANOVAs will be used for interval data and Chi square for nominal data; effect size differences will be reported.

To assess trial effects, ITT analysis will provide an unbiased estimate of the impact of the intervention [58] comparing participants assigned to the KIND Challenge with those in the control group. ITT includes every participant that is randomised and ignores adherence and compliance and anything that happens post randomisation. Thus, participants are analysed as randomised, reducing bias and with the purpose of ensuring groups differ only on the intervention being compared. ITT, therefore, represents real practical scenarios in which lack of adherence and compliance would naturally be encountered. ITT will be applied to H1–4. ITT, however, suffers from issues of non-compliance because participants assigned to the intervention may not engage with it and, thus, would bias and dilute impact of the intervention. Therefore, H7 aims to explore how compliance, adherence, and engagement with the KIND Challenge intervention moderate impact on outcomes; H8 will assess the impact of compliance on outcomes, using Complier Average Causal Effects (CACE).

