### Outcomes analysis

An ITT analyses approach, using linear multiple regression modelling in Mplus 8.3, will be employed. A KIND Challenge intervention effect can be noted if the coefficients associated with the trial group variable are statistically significant and effect size recorded.

A model building approach will be used. Model 1 will include loneliness as the outcome variable, with explanatory co-variates gender, age group, baseline loneliness respectively. The target variable trial group (KIND Challenge versus control group) will be added with control group as the reference group (coded 0). Sensitivity analysis will be conducted to determine if effects are robust and are maintained once additional explanatory variables are controlled for.

Model 2 will build in additional secondary and mental health explanatory variables, e.g., baseline social isolation, depression, social anxiety, stress, quality of life, positive affect, given their known associations with the response variable.

Model 3 will build in additional community explanatory variables, e.g., baseline levels of Nextdoor platform activity (both active and passive use), baseline community engagement, Pre-KIND Challenge neighbourhood contact and previous kindness activity engagement, and neighbourhood relationship quality variables of (a) social cohesion and trust, (b) perception that their neighbourhood is improving, (c) higher importance around getting to know their neighbours, (d) feelings of ambivalence towards their neighbours, supportive, aversive, or ambivalent neighbour network classification, (e) neighbourhood conflict, and (f) number of neighbourhood contacts.

Model 4 will build in controlling for COVID-19 climate by asking respondents the number of government restrictions imposed (from a list of 13 types of restrictions).

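### For drop-outs, FIML on the planned H1 regression gives the complete-case estimate, so FIML itself does not reduce attrition bias as the protocol claims

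*Protocol article*

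**What the plan says.** All references are to the protocol article.

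- **Outcomes analysis** sets the H1 model as a linear regression: "Model 1 will include loneliness as the outcome variable, with explanatory co-variates gender, age group, baseline loneliness respectively". Trial group is then added. Further baseline covariates enter in Models 2 to 4, introduced as a check that effects are robust.
- **Recruitment and enrolment** places the baseline survey before randomisation.
- **Missing data** sets a two-branch rule: "if less than 5% of data are missing a complete case analysis will be undertaken"; above 5%, FIML is used if data are missing at random (MAR). A logistic regression will look for predictors of missingness, but nothing says that they enter the FIML model. The section closes by saying that FIML will "include both partially and completely observed cases of all participants in the analysis, thereby reducing the bias associated with attrition".
- **Statistical methods** states that "ITT includes every participant that is randomised and ignores adherence and compliance".
- **Feasibility** accepts drop-out just under 40%.

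**The concern.** The protocol credits FIML with bringing every randomised participant into the analysis and thereby lowering attrition bias. That can happen when the likelihood contains something observed on drop-outs that informs their missing outcome beyond the covariates already in the regression, such as auxiliary variables or other post-baseline waves. Model 1 as described has neither. A reader of the results would then believe that attrition had been addressed by a step that leaves the arm estimate unchanged.

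Attrition that differs by arm is plausible here. The arms are unblinded, KIND participants get weekly reminder emails, and waitlist participants get a single email. If those who leave KIND differ in baseline mental health from those who leave the waitlist, Model 1 does not adjust for it.

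**Working it through.** **1. The plan's own figure.** Inputs from Sample size: "for a projected sample of 1500 participants per country and with up to 20 co-variates for the primary outcomes of loneliness"; "Power was set at 0.80 and an Alpha threshold of 0.05"; and "for a conservative estimate the lowest correlations for each outcome are used", so r = 0.35 and R² = 0.1225. Allocation is 1:1 (P = 0.5). Two-sided testing is assumed.

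MDES = (t(0.975, df) + t(0.80, df)) × √[(1 − R²) / (P(1 − P)N)], with df = 1500 − 20 − 2 = 1478.

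= (1.9616 + 0.8419) × √(0.8775 / 375) = 2.8035 × 0.04837 = 0.1356.

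This rounds to the stated value, "a minimum detectable effect size (MDES) for a trial effect is .14 in an intention-to-treat (ITT) analysis". It serves below as a yardstick and is not in dispute.

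**2. Why FIML equals complete-case here.** Let y be the post-intervention score, x the arm and baseline covariates, and b the regression coefficients. A participant with y observed contributes f(y | x, b). A drop-out contributes ∫ f(y | x, b) dy = 1, which does not involve b. Only completers determine the arm coefficient.

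**3. Numerical check.** Model 1 was fitted by joint-normal maximum likelihood (EM) and by least squares on completers. There were 200 simulated trials of N = 1500 per scenario, a true effect of −0.14 SD and roughly 40% to 46% of outcomes missing. The largest difference in any coefficient was about 2e-10, which is convergence error.

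| Missingness depends on | Complete-case | FIML | FIML, depression as auxiliary | Complete-case, depression as covariate |
|---|---|---|---|---|
| Model 1 variables | −0.141 | −0.141 | −0.142 | −0.142 |
| Baseline depression, KIND only (log-odds 1.0 per SD) | −0.187 | −0.187 | −0.139 | −0.140 |

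The simulation assumes a correlation of 0.6 between depression and baseline loneliness.

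**4. Size of the bias in Model 1.** Null true effect, N = 2,000,000, slope of outcome on depression 0.2 to 0.3 SD, drop-out log-odds 0.5 to 0.8 per SD of depression. None of these inputs is in the protocol.

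| Drop-out, KIND / waitlist | Selection on depression | Depression–loneliness correlation | Bias (SD) |
|---|---|---|---|
| 40% / 25% | KIND only | 0 | −0.038 to −0.083 |
| 40% / 25% | KIND only | 0.6 | −0.024 to −0.055 |
| 40% / 25% | same in both arms | 0.6 | −0.009 to −0.020 |
| 33% / 33% | same in both arms | 0.6 | about 0 |

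The first row is 0.038/0.14 = 27% to 0.083/0.14 = 59% of the MDES. With depression in the model, the bias was at most about 0.004 SD throughout, which is within simulation error.

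**5. Skipped baseline items.** If 2%, 5% or 10% of participants also lack baseline loneliness, FIML recovers about 16, 40 or 80 of roughly 800 observed outcomes, and the SD of the arm estimate falls by about 3%. These are respondents with a missing covariate, not drop-outs.

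**6. Precision.** Because drop-outs add nothing, 40% loss leaves 900 per country: MDES = (1.9627 + 0.8420) × √(0.8775 / 225) = 2.8047 × 0.06245 = 0.175, and power at 0.14 is 61%. The 40% is the feasibility limit, not an expected rate.

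**The case against.** **Models 2 and 3 already hold most of the remedy.** They add baseline depression, social anxiety, stress, quality of life, positive affect, isolation and the neighbourhood variables. These are nearly all the missingness predictors that the protocol lists, and the power calculation allows for up to 20 covariates. This stands. A reader might infer that the plan leaves attrition bias unaddressed, and the document does not support that: the larger models deal with attrition that depends on their covariates. What remains is that this gain comes from the covariates, is the same under complete-case analysis, and sits in models presented as sensitivity analyses.

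**FIML is not empty in this plan.** The Serious adverse events section lets participants skip questions. If 20 covariates were each 1% to 2% missing independently (an assumption), listwise deletion would lose 1 − 0.99²⁰ = 18% to 1 − 0.98²⁰ = 33% of participants. FIML that models the covariates keeps those with an observed outcome. This stands, but it does nothing for drop-outs.

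**The upper bias figure is an adverse case.** It needs selection in one arm only and unequal loss. This stands. A reader might take 27% to 59% of the MDES as the expected bias; the protocol gives no drop-out mechanism or arm-specific rate to support that.

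**An analysis for data not missing at random may be in the statistical analysis plan.** That plan is not shown, and such analyses and lists of auxiliary variables are commonly left to it. A reader might count their absence as an error; it is not one.

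**Conclusion.** The sentence crediting FIML with reducing attrition bias is wrong for drop-outs in the H1 analysis as described. The equality with complete-case analysis is algebraic. It rests on two conditions: only the outcome is missing, and no auxiliary variables or further post-baseline waves are in the model. The first follows from the timing of the baseline survey, apart from skipped items. The second is how the protocol describes the analysis, although it does not exclude auxiliaries.

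The consequence for the Model 1 estimate ranges from about zero to about −0.08 SD (towards benefit), depending wholly on assumed mechanisms. This should be fixed, but it does not invalidate the design, because adjustment for the main likely predictors is already planned in the larger models.

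**What to change.** - **H1 estimate.** Fit FIML with the baseline mental-health, isolation and neighbourhood scores, and the predictors found in the missingness regression, as auxiliary variables. Multiple imputation by arm with the same variables, or naming the covariate-rich model as primary, would also do.
- **Post-baseline scores.** Use them as auxiliaries only if modelled by arm, because waitlist waves after T2 follow that group's own exposure to KIND.
- **Wording.** State that the reduction in attrition bias depends on the auxiliary variables or covariates, and that FIML alone recovers only respondents with skipped covariate items. The 5% rule can stay: for drop-outs both branches give the same Model 1 estimate.
- **Useful addition.** A delta-adjusted analysis for H1, by arm. FIML is conditional on MAR, and a regression of missingness on observed data cannot verify MAR. For scale, if 40% of KIND drop out and are 0.2 SD lonelier than predicted, the bias is 0.40 × 0.2 = 0.08 SD towards benefit.

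The cost is a few lines of Mplus code, one sentence of text and, if the addition is taken up, one sensitivity table. The baseline variables are already collected, so no new data are needed.
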